## Abstract

**Background:**

The current randomized controlled trial seeks to evaluate whether providing access to an Internet intervention for problem drinking in addition to an Internet intervention for problem gambling is beneficial for participants with gambling problems who do or do not have co-occurring problem drinking.

**Methods:**

Potential participants will be recruited online via a comprehensive advertisement strategy, if they meet the criteria for problem gambling. As part of the baseline measures, problem drinking will also be assessed. Eligible participants (*N* = 280) who agree to partake in the study and to be followed up for 6 months will be randomized into one of two versions of an Internet intervention for gamblers: an intervention that targets only gambling issues (G-only) and one that combines a gambling intervention with an intervention for problem drinking (G + A). For problem gamblers who exhibit co-occurring problem drinking, it is predicted that participants who are provided access to the G + A intervention will demonstrate a significantly greater level of reduction in gambling outcomes at 6 months compared to those provided access to the G-only intervention.

**Discussion:**

This trial will expand upon the current research on Internet interventions for addictions and inform the development of treatments for those with co-occurring problem drinking and gambling.

**Trial Registration:**

ClinicalTrials.gov, NCT03323606. Registered on 24 October 2017.

**Electronic supplementary material:**

The online version of this article (10.1186/s13063-018-2672-x) contains supplementary material, which is available to authorized users.

## Background

A challenge for addressing problem gambling, as with many addictions, is that the majority of people with gambling concerns never seek treatment [1–3]. To address these unmet needs, self-directed treatments have been developed, with the initial efforts focusing on bibliotherapy, and more recently, on Internet interventions. While there is a fairly strong evidence base for bibliotherapy [4–7], the evidence on Internet interventions is still emerging [8–10].

Parallel to the development of self-help interventions for problem gamblers has been the growing recognition that people experiencing gambling problems often experience other, co-occurring mental health concerns [11–16], including problem drinking [13, 14, 17–20]. An important issue to address in delivering self-help interventions (and, indeed, the delivery of face-to-face therapy) is whether there is an advantage in simultaneously providing interventions for mental health concerns alongside the provision of a gambling intervention, in particular among people who are specifically seeking help for their gambling concerns.

This protocol outlines the second of two randomized controlled trials (RCTs) addressing this question. The first trial examined the benefits of combining a gambling Internet intervention with an already validated online intervention for mood and anxiety [9]. The current trial uses a similar approach to test the benefits of combining the same online gambling intervention with a brief intervention for problem drinkers.

### Major research questions

The proposed trial will compare the efficacy of two Internet interventions: an intervention that just targets gambling issues (G-only) versus one that contains an intervention for problem drinking in addition to an intervention for gamblers (G + A). Outcome variables for gambling will measure the reduction in gambling severity and frequency of gambling. The outcome for a reduction in alcohol use will be measured by the reduction in the frequency of drinking during the past week. The primary hypotheses are:**Hypothesis 1:** For problem gamblers with co-occurring problem drinking, it is predicted that participants provided access to the G + A website will display significantly reduced gambling outcomes at the 3- and 6-month follow-ups compared to those provided access to the G-only website. For problem gamblers without co-occurring problem drinking, there will be no significant difference between those provided access to the G-only and G + A websites at the 3- and 6-month follow-ups.**Hypothesis 2:** For problem drinkers, it is predicted that participants provided access to the G + A website will display significantly reduced drinking outcomes at the 3- and 6-month follow-ups compared to those provided access to the G-only website. For participants who are not problem drinkers, there will be no significant difference in drinking between those provided access to the G-only and G + A websites at the 3- and 6-month follow-ups.**Hypothesis 3:** Problem gamblers with co-occurring problem drinking who receive the G + A intervention and reduce the amount they drink between the baseline and 3-month follow-ups will display significantly improved gambling outcomes at the 6-month follow-up compared to problem drinkers who receive the G + A intervention but experience no decrease in their drinking.

Follow-ups at 3 and 6 months were chosen as it is unknown whether the intervention will have the predicted impact, and we wished to optimize the possibility of finding an effect by employing a short-term follow-up.

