### Power analysis

Efforts will be made to recruit a total sample of 280 participants, and we anticipate that 224 participants will be successfully followed up at 6 months (i.e., estimated 20% attrition based on previous research of online interventions, albeit targeting hazardous alcohol use) [40]. This sample size will provide sufficient power to conduct the proposed statistical analyses necessary to test the aforementioned hypotheses. Based upon previous data collected by Hodgins et al. [4, 6] on gambling frequency and NODS scores, and assuming that a correlation of 0.5 exists between baseline and follow-up measures, then power = .0.80 and α = .05. This sample size is sufficient to detect a difference of at least two gambling days per month between both experimental conditions in both the 3- and 6-month follow-up periods. Smaller differences in gambling days per month may not be clinically meaningful. Similarly, the proposed sample size will also be sufficiently powered to detect a 1-point difference of NODS scores at the 6-month follow-up. Calculations are based upon a repeated measures ANOVA model (G.Power 3.1.9).

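### Hypotheses 1 and 2 predict a non-significant result in participants without problem drinking, but at this sample size that result would not show that the alcohol module has no effect in them

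*Protocol article*

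**What the plan says.** The section on major research questions introduces Hypotheses 1 to 3 with "The primary hypotheses are". The first sentence of Hypothesis 1 predicts better gambling outcomes with G + A in problem gamblers who are also problem drinkers. The second reads "For problem gamblers without co-occurring problem drinking, there will be no significant difference between those provided access to the G-only and" G + A sites, at 3 and 6 months. Hypothesis 2 has the same form for alcohol: "For participants who are not problem drinkers, there will be no significant difference in drinking between those provided access" to either site.

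The other relevant statements in the protocol article are:

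- **Power analysis:** this section plans for 280 participants, with 224 expected to be reached at 6 months. It gives 80% power at α = 0.05 for a difference of two gambling days per month between the two conditions, and adds "Smaller differences in gambling days per month may not be clinically meaningful". It also names a detectable NODS difference of 1 point. It gives no standard deviation, and nothing for drinks per week.
- **Participants:** about half the sample is expected to have co-occurring problem drinking.
- **Baseline survey:** problem drinking is an AUDIT score of 8 or more.
- **Data analysis:** Hypotheses 1 and 2 are analysed with random-intercept linear mixed models. Interactions with baseline severity of gambling and drinking are listed among exploratory models.

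**The concern.** The second sentence of each hypothesis is met by a failure to reject. Noise, dropout and a small subgroup all make that outcome more likely, whatever the true effect. A non-significant superiority test is compatible with no effect and also with an effect the trial would regard as worthwhile.

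The two sentences of each hypothesis also invite a contrast: significant in problem drinkers, not significant in the rest. Two separate test results do not test the difference between two effects.

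This bears on the purpose of the trial. The abstract and discussion ask whether the alcohol module helps gamblers with and without problem drinking, and the discussion hopes to inform the matching of treatment to need. A matching conclusion needs evidence that the effects differ. As worded, the trial could report that the module makes no difference to gamblers without problem drinking when the data fit a benefit of the size it was powered for.

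**Working it through.** **Inputs from the protocol article.** 280 recruited, 20% attrition, 224 followed up; power 0.80, α 0.05; difference of 2 gambling days per month (Power analysis); about 50% problem drinkers (Participants).

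**Assumptions.** Two-sided test, 1:1 allocation, normal approximation, the same variance in both drinking subgroups, and the stated power applying to the whole followed sample.

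**1. The plan's own figures.** 280 × (1 − 0.20) = 224, which matches. The detectable difference cannot be reproduced without a standard deviation. The standard error that makes the statement true can be recovered:

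SE(whole sample) = 2 / (1.960 + 0.842) = 2 / 2.802 = 0.714 days.

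With 112 per arm this corresponds to an effective SD of 5.34 days. The results below depend only on the ratio of effect to SE, so they do not depend on the SD.

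**2. Participants without problem drinking.** Half of 224 is 112, or 56 per arm.

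SE(half) = 0.714 × √2 = 1.010 days.

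**3. Chance that a true 2-day effect is non-significant at one time point.** The standardised effect is 2 / 1.010 = 1.981.

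Power = Φ(1.981 − 1.960) = Φ(0.021) = 0.508, so the miss rate is 0.492.

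Under no effect the chance of non-significance is 0.95. A non-significant result is therefore only about 0.95 / 0.492 = 1.9 times as likely under no effect as under the 2-day effect. Repeated-measures ANOVA variants with correlation 0.5 give subgroup power of 0.49 to 0.51.

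**4. Non-significance at both follow-ups.** With an assumed correlation of 0.5 between the two test statistics, the bivariate normal probability is 0.325 under the 2-day effect and 0.909 under no effect.

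**5. Precision.** The 95% half-width is 1.96 × 1.010 = 1.98 days. Because 2 − 1.98 = 0.02, any observed difference in favour of G + A above about 0.02 days leaves a 2-day benefit inside the interval. The 90% half-width is 1.645 × 1.010 = 1.66 days.

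**6. Equivalence within ±2 days when the true difference is zero.**

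Power (90% interval) = 2Φ(1.981 − 1.645) − 1 = 0.26.

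**7. The interaction.** Comparing two independent halves, SE = √2 × 1.010 = 1.428 days. Power to detect a 2-day difference between the subgroup effects is about Φ(2 / 1.428 − 1.960) = Φ(−0.56) = 0.29.

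**8. Sensitivity, one time point, true 2-day effect.**

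| Share without problem drinking | Miss rate | 95% half-width (days) | Equivalence power |
|---|---|---|---|
| 30% | 66.5% | 2.55 | 0% |
| 40% | 57.5% | 2.21 | 10% |
| 50% | 49.2% | 1.98 | 26% |
| 60% | 41.7% | 1.81 | 40% |
| 70% | 35.0% | 1.67 | 52% |

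If the stated power had been meant for each drinking subgroup, the miss rate would be 20%, the half-width 1.96 × 0.714 = 1.40 days and the equivalence power 75%.

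**9. Hypothesis 2.** With no effect size for drinks per week, steps 1 to 8 cannot be repeated. Only the logical point carries over.

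**The case against.** **It is only a prediction.** A reader might infer that the plan declares a non-significant result to be confirmation of no effect. It does not say so, and the abstract states only the superiority prediction in problem drinkers. That limits the charge. Still, the sentence stands among the primary hypotheses and is worded as a test outcome, so non-significance is the only result that agrees with it.

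**Comparison of two p-values.** A reader might also infer that the analysis will be separate subgroup tests set side by side. The data analysis section says only that mixed models compare groups. The exploratory interactions concern drinking severity, which need not be the AUDIT grouping behind the hypotheses. Model terms may be specified in a fuller document. What stands is that the wording invites the comparison. If the module gave the same 2-day benefit in both halves, the contrast would appear at one time point with probability 0.508 × 0.492 = 0.25. Required at both follow-ups (correlation 0.5), it would be about 0.11. These figures are conditional illustrations, because the plan defines no such rule.

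**The numbers are back-solved.** True. The power analysis also claims sufficiency for testing the hypotheses, which are subgroup hypotheses. Its reference to the total sample and to the two conditions makes the whole-sample reading more likely, but the alternative cannot be excluded. Even then one true 2-day effect in five would be missed.

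**More than one outcome and time.** The 49% is for one outcome at one time point. Hypothesis 1 has two primary gambling outcomes and two follow-ups, so a joint requirement lowers it.

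**Margins.** The text ties clinical meaning to 2 days per month, and cautiously. The 1-point NODS value is a detectable difference and is nowhere called a meaningful limit, so it cannot be taken as the plan's equivalence margin.

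**Conclusion.** The point holds as a fault in the wording of Hypotheses 1 and 2, with consequences for what the trial may conclude. Non-significance in participants without problem drinking would not be evidence of no effect, and its contrast with a significant result in problem drinkers would not show that the effects differ.

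For gambling days, a true 2-day effect in that subgroup would be missed about half the time at a single time point and about a third of the time at both follow-ups. The single-time-point figure runs from 35% to about 66% as the share without problem drinking falls from 70% to 30%, and drops to 20% if the stated power was meant per subgroup. All of this rests on the two-sided, 1:1 and whole-sample assumptions. For Hypothesis 2 the fault is logical only and has no size.

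The documents do not support the stronger statement that the plan commits itself to reading non-significance as proof, or to comparing subgroup p-values.

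**What to change.** 1. Replace the second sentence of Hypotheses 1 and 2 with an estimation statement: the arm difference and its confidence interval in participants without problem drinking will be reported at 3 and 6 months, and absence of a difference will not be concluded from non-significance alone.
2. Base any claim that the benefit is confined to, or larger in, problem drinkers on the interaction of arm with baseline problem drinking (AUDIT 8 or more) in the primary mixed model.
3. If a claim of no meaningful difference in gambling days is wanted, require the confidence interval, at a level fixed in advance, to lie within ±2 days per month, the value in the power analysis. Margins for NODS and for drinks per week would have to be justified separately.

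**Cost.** Two sentences and one reporting rule change. The AUDIT is already collected, and sample size and conduct are untouched. The permitted conclusion becomes weaker: under the assumptions above, power is about 29% for a 2-day interaction and about 26% for equivalence within ±2 days. The report should state this low power.

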#### Baseline survey

The baseline survey will assess demographic characteristics (e.g., age, sex, education, marital status, income, and employment status), clinical characteristics (such as gambling frequency and severity, prior treatment use, problem drinking, illicit drug use in the past year, mental health issues, i.e., depressive/anxiety symptoms and general psychological distress), and quality of life (i.e., using the World Health Organization Quality of Life 8-item survey [29]).

The severity of problem gambling will be measured using the past year PGSI and the past 3-month version of the NORC DSM-IV Screen for Gambling Problems (NODS), which indicates DSM-IV defined severity [30, 31]. The NODS has been previously employed within a 1-year follow-up study to assess brief treatment and its utility as an outcome measure [32]. Additionally, the mean number of days gambled in the past 3 months, the amount spent on gambling, and forms of gambled engaged in will be assessed. The use of treatment services for gambling concerns will be measured by asking participants to identify services accessed from a comprehensive list of treatment forms, as used in previous studies [4, 6]. Lastly, participants will also be asked to identify a treatment goal (quit or reduced gambling) and their perceived success in achieving that goal over the following 3 and 6 months on a Likert scale ranging from 0 “not at all” to 10 “extremely.” The primary outcome variables for gambling will be the NODS and number of days gambled.

Hazardous alcohol consumption will be measured using a past 3-month version of the Alcohol Use Disorders Identification Test, with the frequency of heavy drinking occasions modified for female and male participants (i.e., five or more drinks for males and four or more drinks for females) [33]. A score of 8 or more will indicate problem drinking. The primary outcome variable for alcohol consumption will be number of drinks consumed in a typical week.

The severity of depressive and anxiety symptoms will be measured using the Patient Health Questionnaire 9-item scale (PHQ-9) [34] and the Generalized Anxiety Disorder 7-item scale (GAD-7) [35], respectively. In addition, general psychological distress will be measured using the Kessler 10 questionnaire (K10), as this measure has been found to be responsive to change over time. The K10 has been well validated and is appropriate for self-administration, as it is brief, simple, and easy to comprehend [36, 37].

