### Data analysis

The two primary hypotheses of this study, which focus on comparing outcomes between groups for gambling and drinking respectively, will be analyzed using linear mixed-effect models with random intercepts. This will allow us to use all available participant data within the models, employing a restricted maximum likelihood to handle missing data. Separate analyses will be conducted for each primary outcome variable (i.e., NODS score, mean number of day gambled in the past month, and, for drinking, the number of drinks consumed in a typical week). For secondary analyses, mixed-effects models will be conducted to examine the effect of moderators on primary variables, that is, additional fixed-effect interactions will be included in exploratory models (e.g., extent of intervention use, participants’ sex, severity of gambling and drinking at baseline, and co-occurrence of mental health concerns). In addition, secondary analyses will also examine predictors of treatment use, as well as the effect of accessing treatment on primary outcomes. The third hypothesis, comparing the potential moderating effect of reductions in drinking on gambling severity, will be examined using Hayes’s Process macro. This method uses a state-of-the-art regression-based conditional process approach [41] to estimate covariances, variances, and means. Missing data will be handled using a maximum likelihood approach. Finally, we will examine whether changes in quality of life are related to improvements in gambling outcomes.

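### Hypothesis 3 splits G + A problem drinkers at zero change in self-reported drinking; the size of the reduction is discarded and the two groups differ in baseline drinking by construction

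*Protocol article*

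**What the plan says.** In Major research questions, one Hypothesis 3 group is the G + A problem drinkers who "reduce the amount they drink between the baseline and 3-month follow-ups". The other is given by the phrase "compared to problem drinkers who receive the G + A intervention but experience no decrease in their drinking". No minimum reduction is set, so the two groups exhaust the subgroup and the cut lies at zero change.

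Under Baseline survey, membership of the subgroup rests on the AUDIT: "A score of 8 or more will indicate problem drinking". The drinking measure is self-reported: "The primary outcome variable for alcohol consumption will be number of drinks consumed in a typical week". Hypothesis 3 does not name its measure; I read the amount drunk as this outcome.

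Under Data analysis, Hypothesis 3 is described as "comparing the potential moderating effect of reductions in drinking on gambling severity, will be examined using Hayes’s Process macro", a "regression-based conditional process approach". That section neither repeats the two-group split nor says that the reduction is a continuous score.

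The Power analysis section gives detectable differences only between arms. It gives no power figure for Hypothesis 3.

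**The concern.** A split at zero treats a fall from 30 to 29 drinks like a fall from 30 to 5, and treats 30 to 29 and 30 to 30 as opposites. Three consequences follow.

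- **Information is lost.** If larger reductions go with better gambling outcomes, the split cannot use that.
- **Membership is partly noise.** Near zero change, ordinary fluctuation in a self-report decides the label. The subgroup is also selected on a high baseline score, so some will report fewer drinks later without real change.
- **The groups are unequal at the start.** Those who reported more at baseline have more room to fall, so reducers begin at a higher drinking level whatever the intervention does.

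At stake is whether a real link between drinking at 3 months and gambling at 6 months is found, and whether the comparison can be read without baseline drinking mixed into it.

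**Working it through.** **Inputs from the protocol.** 280 recruited, 20% attrition, 224 followed up, about 50% problem drinkers, two arms, and "assuming that a correlation of 0.5 exists between baseline and follow-up measures". The attrition arithmetic reproduces: 224/(1 - 0.20) = 280. The stated power of 0.80 cannot be reproduced, because no SD is given, and it concerns the arm comparison in any case.

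**Assumptions.** 1:1 allocation; two-sided 0.05; normal scores; the 0.5 correlation, stated in the context of gambling measures, applied to drinks; problem drinkers as the upper half on AUDIT; AUDIT-drinks correlation c of 0.5 or 0.7, acting on 3-month drinks only through baseline drinks; no mean change in the whole sample; standardized slopes of 0.3 and 0.4.

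**1. Sample.** 280 × 0.5 × 0.5 = 70 randomized; 70 × 0.8 = 56 followed up.

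**2. Share labelled reducers with no treatment effect.** Mean baseline drinks in the upper AUDIT half is 0.798c SD, and the 3-month mean is half of that. The mean fall is 0.20 SD (c = 0.5) or 0.28 SD (c = 0.7), and the SD of the fall is 0.98 or 0.96. Φ(0.20/0.98) = 58%; Φ(0.28/0.96) = 61%. Symmetry would give 50%. If AUDIT correlates equally with baseline and 3-month drinks, the share is 50%.

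**3. Baseline gap.** The correlation of baseline drinks with the fall is √((1 - 0.5)/2) = 0.5. Without selection, the gap between the two groups is 2 × 0.798 × 0.5 = 0.80 SD. With AUDIT selection, simulation gives 0.68-0.69 SD (c = 0.5) and 0.57-0.58 SD (c = 0.7). If AUDIT correlates equally with both drinks reports, the gap stays at 0.80 SD.

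**4. Power at n = 56.** Simulated; repeated runs differ by about one to three points.

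| Gambling follows | Slope | Split at zero, unadjusted | Continuous 3-month drinks, adjusted for baseline drinks |
|---|---|---|---|
| 3-month level | 0.3 | 15-17% | about 50% |
| 3-month level | 0.4 | 26-28% | 77% |
| Change | 0.3 | 39-43% | 48-50% |
| Change | 0.4 | 66% | 76-78% |

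Hand check at slope 0.3, ignoring selection:

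- Split, level model: the groups differ by 0.80 SD in 3-month drinks, so by 0.3 × 0.80 = 0.24 SD in gambling. 0.24 × √56/2 = 0.90; Φ(0.90 - 1.96) = 14%.
- Split, change model: the groups differ by 2 × 0.798 = 1.60 SD in change, so by 0.48 SD in gambling. 0.48 × √56/2 = 1.80; Φ(1.80 - 1.96) = 44%.
- Adjusted continuous term, either model: 0.3 × √0.75 × √56/√(1 - 0.09) = 2.04; Φ(2.04 - 1.96) = 53%, slightly above the simulation, which uses the t distribution.

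**5. The cut on its own.** Cutting a normal change score at zero multiplies its correlation by φ(m)/√(p(1 - p)), where m is the mean fall in SD units and p the share of reducers. That is 0.798 at p = 50% and 0.700 at p = 80%, so 0.64 to 0.49 of the information remains. Power for a correlation ρ is Φ(atanh(ρ)√53 - 1.96). At ρ = 0.37 it is 0.81 for the continuous score, and 0.60 (p = 50%) to 0.49 (p = 80%) after the cut.

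**6. Misclassification.** If the change score has reliability 0.8, 0.6 or 0.4 (assumed), about 13-15%, 19-22% or 24-28% of participants fall on the wrong side of zero.

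**The case against.** The strongest reply is that the Data analysis section, not the hypothesis sentence, governs the test. It names a regression method and no cut-off; regression takes a continuous term and covariates, and the coding of a predictor can be left to an analysis plan. This stands in part: the protocol does not commit the analysis to the split, and a reader should not infer that it does. But regression takes a binary term equally well, and the only contrast printed is the two-group one.

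The power comparison also changes several things at once: cut against continuous, unadjusted against adjusted, change against level. Under the level model at slope 0.3, a continuous change score without baseline adjustment has only 23-27% power, so the cut explains 7-9 points of a gap of about 32. Under the change model at slope 0.3, continuous change reaches 57-60%, better than the proposed adjusted model. The adjusted model is still the safer choice: it holds about 50% under both models and contains the change model as a special case. At slope 0.3 it too misses about half of real links.

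A reader might infer that most of the power is lost. That holds only under the level model, and the protocol gives no basis for preferring that model; the hypothesis speaks of reduction. A reader might also infer that noise and regression to the mean decide membership. The figures show influence: 58-61% labelled reducers against 50%, and 13-28% misplaced under assumed reliabilities.

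Finally, Hypothesis 3 is a within-arm question, handled apart from the two arm comparisons. Neither of those is affected.

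**Conclusion.** The point holds as a weakness in how Hypothesis 3 is defined. The printed contrast has no minimum reduction, discards magnitude, and compares groups that start about 0.6 to 0.7 SD apart on drinks. Against the adjusted continuous model, the unadjusted split gives up about 33 to 51 points of power if gambling follows the 3-month level, and about 5 to 12 points if it follows the change.

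The baseline gap is the firmest part: it appeared under every correlation pattern tried. The power figures depend on the assumptions listed, and normality is doubtful for drink counts. The change is worth making, but it does not touch the randomized comparisons.

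**What to change.** State in Hypothesis 3, and again under Data analysis, that among G + A problem drinkers the 6-month gambling outcome is regressed on weekly drinks at 3 months as a continuous term, with baseline drinks and the baseline gambling outcome as covariates. Show the any-decrease against no-decrease comparison only descriptively.

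The cost is the wording of the hypothesis and one model line; every variable is already in the baseline and follow-up surveys. The result is then read as a slope and not as a difference between two groups. The analysis remains a non-randomized association within one arm, with modest power at about 56 participants.
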